# Balance Right in Multiple Sclerosis (BRiMS): a guided self-management programme to reduce falls and improve quality of life, balance and mobility in people with secondary progressive multiple sclerosis: a protocol for a feasibility randomised controlled trial

**DOI:** 10.1186/s40814-017-0168-1

**Published:** 2017-07-27

**Keywords:** Secondary progressive multiple sclerosis, Exercise, Self-management, Mobility, Accidental falls, Balance, Quality of life, Feasibility randomised controlled trial

## Abstract

**Background:**

Impaired mobility is a cardinal feature of multiple sclerosis (MS) and is rated by people with MS as their highest priority. By the secondary progressive phase, balance, mobility and physical activity levels are significantly compromised; an estimated 70% of people with secondary progressive MS fall regularly. Our ongoing research has systematically developed ‘Balance Right in MS’ (BRiMS), an innovative, manualised 13-week guided self-management programme tailored to the needs of people with MS, designed to improve safe mobility and minimise falls. Our eventual aim is to assess the clinical and cost effectiveness of BRiMS in people with secondary progressive MS by undertaking an appropriately statistically powered, multi-centre, assessor-blinded definitive, randomised controlled trial. This feasibility study will assess the acceptability of the intervention and test the achievability of running such a definitive trial.

**Methods/design:**

This is a pragmatic multi-centre feasibility randomised controlled trial with blinded outcome assessment. Sixty ambulant people with secondary progressive MS who self-report two or more falls in the previous 6 months will be randomly allocated (1:1) to either the BRiMS programme plus usual care or to usual care alone. All participants will be assessed at baseline and followed up at 15 weeks and 27 weeks post-randomisation.

The outcomes of this feasibility trial include:Feasibility outcomes, including trial recruitment, retention and completionAssessment of the proposed outcome measures for the anticipated definitive trial (including measures of walking, quality of life, falls, balance and activity level)Measures of adherence to the BRiMS programmeData to inform the economic evaluation in a future trialProcess evaluation (assessment of treatment fidelity and qualitative evaluation of participant and treating therapist experience)

**Discussion:**

The BRiMS intervention aims to address a key concern for MS service users and providers. However, there are several uncertainties which need to be addressed prior to progressing to a full-scale trial, including acceptability of the BRiMS intervention and practicality of the trial procedures. This feasibility trial will provide important insights to resolve these uncertainties and will enable a protocol to be finalised for use in the definitive trial.

**Trial registration:**

ISRCTN13587999.

## Background

Multiple sclerosis (MS) affects approximately 100,000 people in the UK [1], with an estimated cost of £1.4 billion/annum to the National Health Service (NHS) and wider society [2]. Although most people start with a relapsing-remitting (RR) disease course, approximately two thirds move to a secondary progressive phase within 8 years [3]. At this point, medical interventions are limited and progression is inevitable [4].

Surveys of people with MS (pwMS) consistently rank mobility as their highest priority and most important yet most challenging daily function [5]. Evaluation of treatments to improve mobility has also been highlighted as one of the top 10 MS research priorities by the James Lind Alliance [6]. Impaired balance and falls are common issues for people with secondary progressive MS (SPMS) and are an important contributory factor to mobility impairment [7, 8]. Approximately 70% of pwMS fall regularly [9, 10], at an average rate of >26 falls/person/year in SPMS [11]. More than 10% of these falls lead to injuries [12] and pwMS are three times more likely to sustain a fracture than the general population [13].

Falling and fear of falling have a profound impact on individuals, leading to activity curtailment, social isolation and a downward spiral of immobility, deconditioning and disability accumulation [14]. There are also substantial economic and social costs related to increasing immobility, impaired balance and falls in pwMS [15]. Costs of health and social care have been shown to increase steeply with increasing disease severity/immobility, underlining the importance of optimising safe mobility for as long as possible [16]. This is particularly relevant given evidence that pwMS are living longer, leading to a rising population living with the disease [17]. This has important implications for resource provision, as highlighted in a national audit of neurological services [18].

The importance of mobility and falls is further emphasised by their consistent prominence in policy documents for long-term neurological conditions [19]. Work suggests that falls may be an early marker of mobility deterioration associated with disease progression [9, 10]. Rehabilitation interventions which improve balance and physical activity and decrease the risk of falls may slow this deterioration, providing a persuasive argument to prioritise provision of effective physical management strategies. However, there is currently minimal evidence-based guidance to inform optimal mobility management and none to inform falls management in people with progressive MS. Whilst evidence is available for older people and those with other neurological conditions, research suggests that translating existing interventions to pwMS is likely to be ineffective [20, 21]. Small, limited duration studies have evaluated single elements of MS balance and falls interventions, individually demonstrating short-term improvements in mobility, balance or falls awareness [22–24], but these elements have not yet been implemented or evaluated collectively. Moreover, no studies have been confined to people with SPMS. This feasibility trial begins to address all these issues.

Healthcare policy prioritises the need to empower and support patients to self-manage [25]. ‘Balance Right in MS’ (BRiMS) is an innovative evidence-based, user-focused, self-management exercise and education programme, designed to improve safe mobility and reduce falls for pwSPMS. It is critical to assess the delivery of this programme and proposed evaluation methods prior to undertaking a definitive trial to assess its effectiveness and cost effectiveness.

Following Medical Research Council (MRC) Guidelines [26], this feasibility trial will aid the planning of an anticipated definitive, multi-centre randomised controlled trial (RCT) which will compare BRiMS plus usual care with usual care alone in improving mobility and quality of life (QoL), and reducing falls in people with SPMS. This feasibility trial will provide the necessary data and operational experience to inform the conduct and finalise the design of a definitive trial so that it can be successfully delivered with confidence. Ultimately, this will add significantly to the evidence by reporting results of a robust RCT of a manualised, complex intervention.

## Methods

### Trial design

This is a pragmatic, multi-centre, feasibility RCT with blinded outcome assessment. Figure 1 shows the planned participant pathway.

**Fig. 1 Fig1:**
[figure not shown]
Participant pathway

### Trial settings

Four healthcare sites will be involved in this multi-centre RCT, which is based in two geographical regions of the UK: South West Peninsula (England) and Ayrshire (Scotland). A full list of study sites is available via www.brims.org.uk.

### Participants

#### Sample size

As this is a feasibility trial, the more usual sample size calculation, based on considerations of power for detecting a between-group clinically meaningful difference in a primary clinical outcome, is not appropriate [27]. Instead, the aim is to provide robust estimates of the likely rates of recruitment and follow-up, as well as provide estimates of the variability of the proposed primary and secondary outcomes to inform sample size calculations for the planned definitive trial. Therefore, we aim to recruit a total of 60 participants across the two regions (40 in the South West and 20 in Ayrshire) over 6 months. An estimated 240 people will need to be screened to achieve this sample size. From other studies in similar settings, we anticipate that retention rates will be approximately 80% [28, 29]. With our intended sample size of 60 participants, we will be able to estimate the overall retention rate with precision of at least ±13%, and if the 6-month follow-up rate is around 80%, this estimate will have precision of around ±10%. Assuming a non-differential 6-month follow-up rate of 80%, this should provide follow-up outcome data on a minimum of 24 participants in each of the allocated trial arms.

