### Randomisation and allocation concealment

The inclusion of group-based elements as part of the intervention necessitates the confirmed participation of a sufficient number of participants within a recruiting site before randomisation occurs. There are four sites where the intervention will be delivered. Once recruited, participants will ideally be randomised in blocks of 10, but the process can accommodate some flexibility within the limits 8–12 participants in each block. Randomisation will be undertaken when a sufficient number of individuals from a recruiting site have consented, indicated that they are able to attend the same BRiMS group (location, timing, should they be randomised to receive it), and complete baseline data have been collected. The decision to declare a block complete will be made by the research therapist in collaboration with the Trial Co-ordinator, Chief Investigator and local UK Clinical Research Collaboration registered Clinical Trials Unit (CTU) (Registration number 31). Randomisation will be undertaken a minimum of 3 and a maximum of 7 days prior to the commencement of the BRiMS programme delivery (for each block).

When the block size from a recruiting site consists of 8–12 participants, the participants will be randomised to the intervention or control group, using block simultaneous randomisation. The randomisation will be 1:1 when the block consists of an even number of participants, and when the block consists of an odd number of participants, the allocation ratio will be in favour of the intervention group in order to maximise recruitment potential and learning opportunities in this feasibility trial. Participants in a block will be numbered in the order in which they were first entered onto the trial website. The randomisation process will follow a strict and auditable protocol. Randomisation will take place after completion of all baseline assessments by the CTU Trial Manager via a secure web-based system. The randomised allocations will be computer-generated by the CTU in conjunction with an independent statistician, in accordance with the CTU’s standard operating procedure. The randomisation list and the programme that generated it will be stored in a secure network location within the CTU, accessible only to those responsible for provision of the randomisation system.

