### Determining progression to the full trial

We shall progress to a full trial application if minimum success criteria are achieved in key feasibility aims and objectives, or if we can identify solutions to overcome any identified issue. These criteria will be finalised in discussion with the Trial Steering Committee, but are likely to include:A minimum of 80% recruitment of the intended 60 participants within the 6-month recruitment windowA minimum of 80% completion rate of key outcome measures (including follow-up)

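### The stated minimum of 24 followed up in each arm is the expected number under exact 30:30 allocation at 80% follow-up, not a minimum

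*Protocol article*

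**What the plan says.** The Sample size section of the protocol article sets the target: "we aim to recruit a total of 60 participants across the two regions". It describes the retention assumption as approximate ("we anticipate that retention rates will be approximately 80" per cent) and attaches sampling error to it: "if the 6-month follow-up rate is around 80%, this estimate will have precision of around ±10" per cent. It then gives the only per-arm yield in the article. Under the condition "Assuming a non-differential 6-month follow-up rate of 80" per cent, it states that "this should provide follow-up outcome data on a minimum of 24 participants in each of the allocated trial arms".

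The abstract's Methods/design paragraph says that participants "will be randomly allocated (1:1) to either the BRiMS programme plus usual care or to usual care alone". The section on randomisation and allocation concealment qualifies this. Blocks are ideally of 10 but may hold 8 to 12 people, and "when the block consists of an odd number of participants, the allocation ratio will be in favour of the intervention group". The reason given there is to maximise recruitment potential and learning in a feasibility trial.

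**The concern.** A minimum is a floor, and a reader planning from this article would take 24 per arm as the least that the trial will deliver. The number is in fact the centre of a distribution. The section allows for sampling error in the overall retention rate, then drops it in the next sentence, where the per-arm yield is given. The calculation also needs 30 people in each arm, while the randomisation section provides for blocks that move the split away from 30:30, always towards the intervention group.

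The per-arm number matters because the study exists partly to estimate outcome variability for the definitive trial, and the Data analysis section plans 95% confidence intervals for the potential intervention effects. The number with follow-up data governs the precision of both.

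**Working it through.** **Inputs.** Total 60, follow-up 80% in both arms and yield 24 per arm (Sample size). Nominal allocation 1:1 (abstract). Blocks of 8 to 12, with odd blocks favouring the intervention group (randomisation section). One assumption is added: participants are followed up independently of one another with true probability 0.80. For odd blocks, the ratio is taken to mean one extra intervention participant per block.

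**1. The plan's own figures.**
- Per-arm yield: (60 / 2) × 0.80 = 24.0, which is the stated 24.
- Precision at 50% retention: 1.96 × √(0.5 × 0.5 / 60) = 12.7 percentage points, which is the stated ±13%.
- Precision at 80% retention: 1.96 × √(0.8 × 0.2 / 60) = 10.1 percentage points, which is the stated ±10%.

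All three reproduce. The fault is the word minimum, not the multiplication.

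**2. Chance variation at 30:30.** The number followed up in one arm is X ~ Binomial(30, 0.80), with mean 24 and standard deviation √(30 × 0.8 × 0.2) = 2.19.
- One given arm: P(X ≥ 24) = 0.607.
- Both arms: 0.607² = 0.368, so at least one arm falls short with probability 0.632.
- A floor that holds with high probability: P(X ≥ 20) = 0.974, and 0.974² = 0.949 for both arms.

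**3. Odd-sized blocks.** Each odd block adds one to the difference between the arms. With k odd blocks the control arm has (60 − k) / 2 people, and k must be even because the total is 60. Listing every set of blocks of 8 to 12 that sums to 60 gives k = 0, 2, 4 or 6. Examples are 10 × 6 for k = 0; 9, 10, 10, 10, 10, 11 for k = 2; 9, 9, 10, 10, 11, 11 for k = 4; and 9, 9, 9, 11, 11, 11 for k = 6.

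| Odd blocks | Split (intervention:control) | Expected control followed up | P(control ≥ 24) | P(both ≥ 24) | P(both ≥ 20) |
|---|---|---|---|---|---|
| 0 | 30:30 | 30 × 0.8 = 24.0 | 0.607 | 0.368 | 0.949 |
| 2 | 31:29 | 29 × 0.8 = 23.2 | 0.463 | 0.338 | 0.939 |
| 4 | 32:28 | 28 × 0.8 = 22.4 | 0.315 | 0.260 | 0.905 |
| 6 | 33:27 | 27 × 0.8 = 21.6 | 0.182 | 0.163 | 0.842 |

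**4. Sensitivity to the true rate, at 30:30.** P(both ≥ 24) is 0.249 at 78%, 0.368 at 80%, 0.507 at 82%, 0.718 at 85% and 0.949 at 90%. Break-even is at about 82%.

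**5. Effect on precision.** The half-width of a 95% confidence interval for a mean difference, in SD units, is t × √(1/n₁ + 1/n₂), with t = 2.013 on 46 degrees of freedom.
- 24 and 24: 2.013 × √(1/24 + 1/24) = 0.581.
- 26.4 and 21.6 (the 33:27 split): 2.013 × √(1/26.4 + 1/21.6) = 0.584, about 0.5% wider.

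**The case against.** The best defence is that the sentence is conditional. If 80% is read as the rate actually observed in each arm, 24 follows exactly at 30:30. The uncertainty is also disclosed nearby: retention is called approximate, the ±10% is given, and the Discussion says that the borrowed retention estimates may not suit people with secondary progressive MS. This is fair as regards the arithmetic, which is correct. It does not rescue the word minimum. Even with exactly 80% observed, any odd block puts the expected control number below 24, and the same article provides for such blocks.

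It is also fair that little depends on the figure. The article disclaims a power calculation, plans no formal hypothesis tests, and bases its likely progression criteria on percentages.

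A reader might infer more than the document supports, in four ways.
- *That 24 is simply more likely missed than met.* This holds for both arms jointly, at a true rate below about 82%. At 30:30 and 80%, a single arm is more likely to reach 24 than not.
- *That the likely progression criterion, a "minimum of 80% recruitment of the intended 60 participants", contradicts the 24.* That criterion describes a smaller sample and is still to be finalised with the Trial Steering Committee. The 24 is stated for the intended 60.
- *That the control arm is bound to be the smaller one, and is the arm that matters most for planning.* Any all-even set of blocks, including the preferred blocks of 10, gives 30:30. The article does not rank the control arm's data above the other arm's, and adherence to the programme can be learned only in the intervention arm.
- *That the odd-block rule should be changed.* The rule is stated openly with a reason, and its cost in precision is negligible.

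**Conclusion.** The point holds as an error in how a sample-size figure is described. The 24 per arm is an expectation that requires exactly 30:30 allocation. At a true 80% follow-up rate, both arms reach it about 37% of the time. If odd blocks occur, the expected control-arm number is 23.2 or 22.4, with 21.6 only if all six blocks are odd. These probabilities assume independent follow-up and the article's own 80%, and they improve quickly if retention is better. The consequence is minor: the overall precision figures that accompany the target of 60 are correct, and the allocation imbalance barely affects the planned intervals. The sentence is nevertheless wrong as written and should be corrected.

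**What to change.** Replace the end of the sentence with wording such as: *an expected 24 participants per arm if allocation is 30:30 (at least 20 in both arms with about 95% probability), with about 22 to 23 expected in the control arm if odd-sized blocks occur.* The 95% belongs to the 30:30 case and should stay attached to it, since it falls as the split widens.

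The cost is one restated sentence. The target of 60, the randomisation procedure, the analysis and the progression criteria need no change on this account.

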### Inclusion criteria

The trial population will comprise individuals with a confirmed diagnosis of MS as has been determined by a neurologist according to revised McDonald’s criteria [30], and who are in the secondary progressive phase.

Participants will:Be aged ≥18 yearsBe willing and able to understand/comply with all trial activitiesScore ≥4.0 ≤ 7.0 on the Expanded Disability Status Scale, i.e. people who have some mobility impairment, but who are ambulant for at least a proportion of the timeSelf-report two or more falls in the past 6 monthsBe willing and able to travel to local sites for blinded outcome assessments and BRiMS programme sessionsHave access to a computer or tablet and to the internet

### Exclusion criteria

Potential participants will be excluded if they:Have relapsed/received steroid treatment within the last month (patient-reported relapse is defined as ‘the appearance of new symptoms, or the return of old symptoms, for a period of 24 h or more—in the absence of a change in core body temperature or infection’) [31]Have had any recent changes in disease-modifying therapies; specifically, if they have ever had previous treatment with alemtuzemab; are within 6 months of ceasing nataluzimab; or are within 3 months of ceasing any other MS disease-modifying drugHave participated in a falls management programme within the past 6 monthsReport co-morbidities which may influence their ability to participate safely in the programme or are likely to impact on the trial (e.g. uncontrolled epilepsy).Are participating in a concurrent interventional study

Identification and recruitment of participants will be via several routes, including identification by healthcare professionals, screening MS databases and promotion via MS support groups and newsletters. This will be supported by National Institute for Health Research (NIHR) Clinical Research Network staff at each site.

### Randomisation and allocation concealment

The inclusion of group-based elements as part of the intervention necessitates the confirmed participation of a sufficient number of participants within a recruiting site before randomisation occurs. There are four sites where the intervention will be delivered. Once recruited, participants will ideally be randomised in blocks of 10, but the process can accommodate some flexibility within the limits 8–12 participants in each block. Randomisation will be undertaken when a sufficient number of individuals from a recruiting site have consented, indicated that they are able to attend the same BRiMS group (location, timing, should they be randomised to receive it), and complete baseline data have been collected. The decision to declare a block complete will be made by the research therapist in collaboration with the Trial Co-ordinator, Chief Investigator and local UK Clinical Research Collaboration registered Clinical Trials Unit (CTU) (Registration number 31). Randomisation will be undertaken a minimum of 3 and a maximum of 7 days prior to the commencement of the BRiMS programme delivery (for each block).

When the block size from a recruiting site consists of 8–12 participants, the participants will be randomised to the intervention or control group, using block simultaneous randomisation. The randomisation will be 1:1 when the block consists of an even number of participants, and when the block consists of an odd number of participants, the allocation ratio will be in favour of the intervention group in order to maximise recruitment potential and learning opportunities in this feasibility trial. Participants in a block will be numbered in the order in which they were first entered onto the trial website. The randomisation process will follow a strict and auditable protocol. Randomisation will take place after completion of all baseline assessments by the CTU Trial Manager via a secure web-based system. The randomised allocations will be computer-generated by the CTU in conjunction with an independent statistician, in accordance with the CTU’s standard operating procedure. The randomisation list and the programme that generated it will be stored in a secure network location within the CTU, accessible only to those responsible for provision of the randomisation system.

After randomisation has taken place, an automatic email will be sent by the CTU to the NHS Therapist leading the BRiMS programme locally and to the relevant Principal Investigator to notify them of each participant’s allocated group. Notification that randomisation has taken place (but *no* details regarding individual participant’s allocated group) will also be sent to the relevant research therapist and to the CI.

Access to the randomisation code and allocation list will be confined to the CTU data programmer; no one else in the trial team will be aware of allocated trial arms until formal randomisation is completed, hence maintaining effective concealment. Following randomisation, only appropriate members of the trial team will be aware of participants’ allocations to intervention or control group; the blinded research therapists will *not* have access to treatment allocation.

